### Statistical Analysis

The statistical analysis of the data will be carried out using SPSS (version 27; IBM Corp). The study population will be described using the background, clinical, and pathological variables to characterize the sample of participants with OSA. The Kolmogorov–Smirnov test will be used to identify the distribution of quantitative variables. For variables with normal distribution measures of central tendency and dispersion will be estimated. For variables with a free distribution mean and IQR will be used. Measures of frequency and percentages will be used for sociodemographic and clinical qualitative variables, as well as those of patient proportion with and without glycemic control, and with and without cognitive impairment. A chi-square test will be used to compare the effect of MD versus SD on parameters of control and uncontrol of metabolic risk indicators. Depending on the data distribution, a Student *t* test will be used to compare quantitative variables with parametric distribution between groups, and a Mann-Whitney *U* test will be conducted for free-distribution variables. A multivariate logistic regression analysis will be performed, including the achievement of metabolic indicator control goals, sleep quality, and quality of life as outcome variables. This analysis will be adjusted for other variables that may be statistically significant in the bivariate analysis, such as sex, age, and comorbidities, among others. Statistically significant differences between groups will be considered when the value of *P*<.05.

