**Inclusion criteria**
Men and womenAged 30-70 yearsDiagnosed with moderate or severe obstructive sleep apneaUse of continuous positive airway pressure (CPAP)

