### Primary Outcomes

The primary objective of this clinical trial is to evaluate the effect of the MD adapted to the Mexican diet versus an SD treatment on metabolic risk indicators in patients with OSA (body weight, fasting glucose, lipid profile, WC, and body composition).

The secondary outcomes are to evaluate the effect of the intervention on:

Sleep quality through ESS.Changes in quality of life through QSQ.Adherence to nutritional therapy intervention through records of meals corresponding to previous and MEDAS questionnaires.

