## Results

The protocol was approved in 2024, and funding is being sought for patient follow-up, patient inclusion, and execution of RCT in 2025. Currently, 50 patients have been recruited, 28 in the group with a Mediterranean Diet Adjusted Using Mexican Food and 27 in the group with an SD. The data analysis with the expected results will be carried out in February 2026.

It is expected that there will be differences in the intervention groups of patients with OSA enrolled in the study: measurement of blood pressure, measurement of sleep variables, measurement of biochemical indicators, anthropometric and body composition measures, measurement of sleep quality, and measurement of quality of life. We expect to find in patients with MD a higher proportion of cardiometabolic indicators in control, compared with patients in the group with SD. We expect to find differences in multivariate analysis in control goals of cardiometabolic indicators, quality of sleep and quality of life of patients.

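### Binary control-goal comparisons take no planned account of whether a patient was already at goal at entry, although eligibility does not require any indicator to be out of goal

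*Protocol article*

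**What the plan says.** **Who may enter.** The inclusion list in Textbox 1 of the protocol article reads: "Men and womenAged 30-70 yearsDiagnosed with moderate or severe obstructive sleep apneaUse of continuous positive airway pressure (CPAP". No glucose, lipid, waist or minimum-BMI threshold appears in it. The metabolic entries among the exclusion criteria all lie at the severe end: BMI above 40, refractory dyslipidemia and familial dyslipidemia.

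**What is measured.** Primary Outcomes names the metabolic risk indicators as "body weight, fasting glucose, lipid profile, WC, and body composition".

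**How the binary outcomes are analysed.** Statistical Analysis states: "A chi-square test will be used to compare the effect of MD versus SD on parameters of control and uncontrol of metabolic risk indicators". It continues: "A multivariate logistic regression analysis will be performed, including the achievement of metabolic indicator control goals, sleep quality, and quality of life as outcome variables". Covariates are chosen as follows: "This analysis will be adjusted for other variables that may be statistically significant in the bivariate analysis, such as sex, age, and comorbidities, among others". Neither the baseline value of the indicator nor control status at entry is named. The Discussion adds recorded CPAP use to the multivariate analysis.

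**How the continuous outcomes are analysed.** The same section says that "a Student *t* test will be used to compare quantitative variables with parametric distribution between groups", with a Mann-Whitney U test otherwise.

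**What result is expected.** The Results section says: "We expect to find in patients with MD a higher proportion of cardiometabolic indicators in control, compared with patients in the group with SD".

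**The concern.** A patient with normal fasting glucose at entry will usually still be normal at 12 months in either arm. In a plain two-by-two table that patient counts as controlled and says little about whether the diet improves glucose. The more such patients there are, the closer the two proportions move together. The share at goal will differ between glucose, each lipid fraction and waist, so each comparison is diluted by a different and unplanned amount. A diet that helps those who need it could then look weak on the very proportions that the Results section expects to differ.

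Control status at entry is also likely to be one of the strongest predictors of control at 12 months. An unadjusted chi-square ignores it. The logistic model admits it only if it is offered to the bivariate screen and passes. The comorbidities mentioned as covariates could stand in for part of it, but that is not the same as planning for it.

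**Working it through.** **Inputs.** From the sample-size paragraph under Study and Population Assignment: 58% v 30% with weight loss, 95% confidence (taken as two-sided 5%), 80% power, 49 per group before losses. The share at goal at entry, c, is not in the documents; 20%, 40% and 60% are assumptions. Borrowing 58% v 30% for patients not at goal is also an assumption.

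**1. The stated sample size reproduces.** With pooled variance and mean proportion 0.44:

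n = [1.96·√(2·0.44·0.56) + 0.8416·√(0.58·0.42 + 0.30·0.70)]² / 0.28² = (1.376 + 0.567)² / 0.0784 ≈ 48.1, rounded up to 49.

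Power at 49 per arm is Φ[(0.28 − 1.96·0.1003)/0.0962] = 81%.

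**2. Dilution in an all-patient chi-square.** If the at-goal share stays at goal in both arms, p′ = c + (1 − c)p, and the difference is 28(1 − c) points. For c = 40%: 0.40 + 0.60·0.58 = 0.748 and 0.40 + 0.60·0.30 = 0.580; power = Φ[(0.168 − 1.96·0.0954)/0.0939] = 42%.

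| c | All patients | Difference | Power, all patients (49 per arm) | Not at goal, per arm | Power, those only |
|---|---|---|---|---|---|
| 0 | 58% v 30% | 28.0 | 81% | 49 | 81% |
| 20% | 66% v 44% | 22.4 | 61% | 39 | 71% |
| 40% | 75% v 58% | 16.8 | 42% | 29 | 58% |
| 60% | 83% v 72% | 11.2 | 26% | 20 | 42% |

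**3. Stratifying by status at entry.** The Cochran-Mantel-Haenszel statistic sums w·d over the strata, with w = n/2 for n per arm in the stratum. Its null variance is Σ w·p̄(1 − p̄), and its variance under the alternative is Σ (n/4)(p₁q₁ + p₂q₂). For c = 40% the strata have 29.4 (not at goal) and 19.6 (at goal) per arm.

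- *Nobody loses control.* The at-goal stratum contributes nothing. The sum is 14.7·0.28 = 4.116, with variances 3.622 and 3.334. Power = Φ[(4.116 − 1.96·1.903)/1.826] = 58%, against 42% for the chi-square.
- *10% lose control in both arms.* The at-goal stratum adds 9.8·0.9·0.1 = 0.882 to each variance. Power = Φ[(4.116 − 1.96·2.122)/2.053] = 49%, against 40%.
- *The diet also protects control (10% v 30% lose it).* The at-goal stratum adds 9.8·0.20 = 1.96 to the sum, giving 6.076, with variances 5.190 and 4.804. Power = Φ[(6.076 − 1.96·2.278)/2.192] = 77%. The all-patient proportions are 0.4·0.9 + 0.6·0.58 = 0.708 and 0.4·0.7 + 0.6·0.30 = 0.460, with power about 71%. Restricting to patients not at goal gives 58%.

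Stratification beats the plain chi-square in all three cases. Restriction beats both when the diet has no effect on keeping control and some control is lost, but is the worst of the three when the diet protects control.

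**4. Chance imbalance at entry.** At c = 40% the between-arm difference in baseline control has standard error √(2·0.4·0.6/49) = 0.099, about 10 points. Randomisation and the 5% level allow for this, so it is noise, not bias. Adjustment removes much of it.

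**The case against.** Much of the opposing case stands.

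- **The binary analysis is not the only one.** The primary indicators are measured quantities, and t or Mann-Whitney tests are planned. A reader might infer that the whole effect is judged on the proportion in control. The document does not say that, so the dilution touches only the chi-square and logistic analyses.
- **The power figures do not describe this trial's planned power.** The 58% v 30% concerns weight loss in the whole of each group, and the trial was never sized on control of glucose or lipids. A reader might infer that 49 per group is wrong. It is not: it reproduces for the outcome it was set for. The share c has no source here and may be small for weight or waist in this population.
- **Achievement could mean new attainment, and a full protocol or analysis plan could say so.** That may settle the logistic outcome. It would not cover the chi-square, which is described as control v uncontrol, or the stated rule for choosing covariates. The point rests on these stated methods combined with the stated eligibility, not on a missing definition.
- **Keeping control is also an effect on metabolic risk.** This is right. A reader might infer that patients at goal should be dropped, or that eligibility must require an abnormal indicator. The objective is the effect in patients with sleep apnea, so broad entry is a legitimate choice, and the third case above shows that dropping those at goal can cost power. The severe-end exclusions are not a fault either.

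**Conclusion.** The point holds for the binary control-goal analyses only. Eligibility allows patients who are already at goal, and the stated chi-square and covariate rule do not plan for that, although baseline values are collected. Under the borrowed 58% v 30%, with the at-goal share staying at goal in both arms, power with 49 per arm would be 61%, 42% or 26% for c of 20%, 40% or 60%, instead of 81%. These figures show direction and rough scale and do not estimate the trial's power. At c = 40%, stratification raises 42% to 58% if nobody loses control, 40% to 49% if 10% lose it in both arms, and 71% to 77% if the diet also protects control. The documents do not support calling the sample size wrong, the eligibility faulty or the continuous comparisons affected. It is a worthwhile and cheap improvement to make before the analysis.

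**What to change.** For each control-goal outcome, state in advance that control status at entry is accounted for in one of two ways:

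- a Cochran-Mantel-Haenszel comparison of the arms, stratified by at goal or not at goal at entry, in place of the plain chi-square; or
- a logistic model in which the baseline value of that indicator is always included, whatever the bivariate screen shows.

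Alongside it, report by arm the proportion attaining the goal among patients not at goal at entry, and the proportion losing control among those at goal at entry.

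**Cost.** No new data are needed, because the indicators are already measured at baseline, and no change to eligibility is needed. The analysis takes slightly more work, and some strata will be small for some indicators, so the separate attainment and loss figures will be imprecise. The change should be fixed before the analysis that the Results section schedules for February 2026.

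### For metabolic indicators with a control goal, up to three between-group tests share one P<.05 rule and none is named as deciding; if any significant test counts, the false-positive chance for one outcome is roughly 7% to 12%, not 5%

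*Protocol article*

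**What the plan says.** The Statistical Analysis section of the protocol article sets out three kinds of between-group comparison that can fall on the same metabolic indicator:

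- **Control status, unadjusted:** "A chi-square test will be used to compare the effect of MD versus SD on parameters of control and uncontrol of metabolic risk indicators".
- **Measured value:** "a Student *t* test will be used to compare quantitative variables with parametric distribution between groups", or, as its substitute, "a Mann-Whitney *U* test will be conducted for free-distribution variables". These two are alternatives and count as one test.
- **Control goal, adjusted:** "A multivariate logistic regression analysis will be performed, including the achievement of metabolic indicator control goals, sleep quality, and quality of life as outcome variables". The adjusters are chosen from the data: "This analysis will be adjusted for other variables that may be statistically significant in the bivariate analysis, such as sex, age, and comorbidities, among others".

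One significance rule closes the section: "Statistically significant differences between groups will be considered when the value of *P*<.05". No comparison is called primary, confirmatory or supportive.

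The Primary Outcomes section lists "body weight, fasting glucose, lipid profile, WC, and body composition" without attaching a test to any of them. The Results section anticipates a larger share of indicators in control under the Mediterranean diet, differences in the measurements themselves, and also this: "We expect to find differences in multivariate analysis in control goals of cardiometabolic indicators, quality of sleep and quality of life of patients".

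**The concern.** Take fasting glucose. After the trial there could be a chi-square P value for controlled versus uncontrolled, a t or Mann-Whitney P value for the glucose level, and a logistic P value for reaching the goal. These address different quantities: a difference in proportions, a difference in means or ranks, and a conditional odds ratio. They can disagree on the same data. Nothing in the article says which one settles whether the diet affected glucose, so a significant result from any of them could be reported as an effect. Under that reading the nominal 5% does not hold even for a single outcome at a single visit.

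This is separate from having several primary indicators. Cutting the list to one outcome would still leave up to three unranked tests on it.

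**Working it through.** **1. What the article points to.** Four places suggest a deciding analysis, and they do not agree:

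- The sample-size paragraph (Study and Population Assignment) uses a difference in proportions with weight loss, 58% versus 30%. This is closest to the chi-square.
- The abstract names only the adjusted logistic regression.
- Primary Outcomes lists measured quantities, which points to the t or Mann-Whitney test.
- Results expects positive findings on all three fronts.

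**2. The plan's own figure.** Inputs: 58%, 30%, 95% confidence, 80% power. Sidedness is not stated; two-sided is assumed. With pooled p = (0.58 + 0.30)/2 = 0.44:

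n = [1.96·√(2·0.44·0.56) + 0.842·√(0.58·0.42 + 0.30·0.70)]² / 0.28² = [1.376 + 0.567]² / 0.0784 ≈ 48.1, rounded up to 49.

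The stated 49 per group is reproduced. It is the size for one test of proportions at 5%.

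**3. Upper reference.** If the tests were independent, P(at least one P<.05) = 1 − 0.95^k: 0.0975 for two and 0.1426 for three. The tests share the same data, so the real figure is lower.

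**4. How strongly they are correlated.** For a normal outcome with a proportion p in control, the large-sample correlation between the t statistic on the value and the chi-square on control status is φ(z_p)/√(p(1−p)). This gives 0.70 at p = 0.20, 0.76 at p = 0.30 and 0.79 at p = 0.44. It is high, but leaves room for one test to reject without the other.

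**5. Null simulations, one outcome at one visit.** The documents give neither the proportion in control nor the covariate strength, so both were varied. Each test alone rejected in about 4% to 6%. At least one of the three rejected as follows:

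- Logistic adjusters selected by bivariate significance, 49 or 60 per group, 20% to 44% in control, 4,000 trials per setting: 7.7% to 8.6% with weak covariates (R² 0 to 0.1), 9.7% to 9.8% with R² 0.3, and 10.5% to 10.7% with R² 0.5.
- Logistic model adjusted for the baseline value, 49 per group, 30% or 50% in control, 5,000 trials per setting: 8.7% to 11.7% for baseline-outcome correlations of 0.3 to 0.9.
- A further run with 49 per group: 7% to 8% with a non-prognostic covariate, and 8% to 11% with baseline correlation 0.3 to 0.7.
- Large-sample correlated statistics, 2 million draws: 8.6% to 10.9% when the quantitative test is on the value, and 10.3% to 12.3% when it is on change from baseline while control status is taken at follow-up.

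The Monte Carlo standard error at 8% with 4,000 trials is √(0.08·0.92/4000) ≈ 0.4 percentage points.

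**6. Where the excess comes from.** In the first set of simulations the quantitative test plus the chi-square alone gave 7.0% to 8.5%. The chi-square plus the logistic model gave about 5% to 8%. The pairing of the value with its dichotomised form therefore accounts for most of the inflation. The logistic model adds under one point when covariates are weak and up to about 2.5 points when they are strong.

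**The case against.** The strongest reply has five parts.

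- **Ranking analyses is often left to an analysis plan, which is not shown.** True, and silence alone would be no finding. But the article is not silent: it fixes three tests under one threshold and states expectations for all of them.
- **No sentence says that one significant test out of three proves an effect.** This stands. A reader might infer that the trial has adopted an any-test-counts rule. The text permits that but does not state it, and the Results section can equally be read as expecting the analyses to agree. The inflation is conditional on that reading.
- **There are hints of an order.** The abstract mentions only the logistic model, and bivariate significance feeds its adjusters, so it could be read as the final step. That is a fair reading but not a designation, and the sample size and the outcome list point elsewhere.
- **Not every indicator need be tested three ways.** This stands. The article gives no control goal for body weight or body composition, and its sentence on quantitative variables does not name the metabolic outcomes. Their use as outcome tests is plausible, because the primary outcomes are listed as measured quantities and Results expects differences in them.
- **A doubling of the error rate depends on assumptions.** This stands. A reader might infer a flat factor of two. The higher figures need strong covariates, a baseline value that the section does not name as an adjuster, or a change-score test. With weak covariates the multiple is nearer 1.4 to 1.7 (7% to 8.5% divided by 5%).

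**Conclusion.** The point holds in a limited form. For metabolic indicators with a control goal, the article plans up to three comparisons at P<.05 and names none as deciding. If any significant one is taken as an effect, the false-positive chance for one outcome at one visit is roughly 7% to 12% instead of 5%. The lower end, about 7% to 8.5%, applies with weak covariates; the upper end needs strong prognostic covariates or a change-score test set beside follow-up control status. These figures assume a normal outcome, two-sided tests, and 20% to 50% in control, none of which the documents supply.

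The documents do not support saying that every metabolic outcome is tested three ways, or that the error rate is simply doubled. Any inflation from having several primary indicators is additional and is not in these figures.

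**What to change.** Before the analysis, which the Results section dates to February 2026, name one deciding analysis per primary outcome in the Statistical Analysis section and align the abstract. A good choice is the between-group difference at 12 months from a linear model with the baseline value as covariate, tested at two-sided .05. For clearly non-normal variables, use a transformation or robust standard errors. Label the chi-square and logistic results supportive and report them as estimates with 95% confidence intervals.

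This must be reconciled with the sample size, which rests on proportions with weight loss. Either keep that comparison of proportions as the deciding test for body weight, or state that the size was derived from it and restate the power for the continuous analysis. As a guide, 49 per group with 80% power detects (1.96 + 0.842)·√(2/49) ≈ 0.57 standard deviations without baseline adjustment. With an assumed baseline correlation of 0.5 this becomes 0.57·√(1 − 0.25) ≈ 0.49. Naming any single analysis would cure the defect; the linear model is preferred because it uses the measured value and a baseline that is already collected.

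The cost is a few lines of text, with no new patients or data. The downside is that a result significant only in a supportive analysis can no longer be claimed as an effect.

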## Methods

### Study and Population Assignment

A randomized, 2-arm clinical trial will be conducted with patients with OSA from the Regional Hospital, Mexican Social Security Institute (Instituto Mexicano del Seguro Social [IMSS]) in Mexico City with a 12-month follow-up.

The sample size was calculated using the formula for difference in proportions, considering a CI of 95% and a power of 80%. Weight loss is expected in 58% of the sample corresponding to the group given an MD adapted to the Mexican population and in 30% of the group consuming a standard diet, as previously reported in the literature. A sample size of 49 patients per group was obtained and, considering losses of 20%, the total number of patients will be 120 [16].

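### No stated analysis of the continuous outcomes conditions on the baseline value, and the choice between means and ranks is left to the data; baseline-adjusted ANCOVA would be more precise with no new data.

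*Protocol article*

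**What the plan says.** Under Primary Outcomes, the protocol article lists body weight, fasting glucose, lipid profile, waist circumference and body composition. The secondary outcomes include the Epworth (ESS) and Quebec (QSQ) sleep questionnaires. All yield quantities or scores, and the follow-up table (Table 2) schedules each at baseline and 12 months in both arms.

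The Statistical Analysis section names these between-group analyses:

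- For control status: "A chi-square test will be used to compare the effect of MD versus SD on parameters of control and uncontrol of metabolic risk indicators".
- For quantitative variables: a Student t "test will be used to compare quantitative variables with parametric distribution between groups", with a Mann-Whitney U test otherwise. The choice depends on the distribution, which a Kolmogorov-Smirnov test is to identify.
- For adjusted analysis: "A multivariate logistic regression analysis will be performed, including the achievement of metabolic indicator control goals, sleep quality, and quality of life" as outcome variables. Covariates are those found significant in bivariate analysis, with sex, age and comorbidities as examples. The Discussion adds CPAP use.

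The threshold is stated as "Statistically significant differences between groups will be considered when the value of *P*<.05". On description, the section says "For variables with a free distribution mean and IQR will be used".

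The sample size, under Study and Population Assignment, uses the "formula for difference in proportions, considering a CI of 95% and a power of 80" per cent. The assumption is that "Weight loss is expected in 58% of the sample" on the adapted Mediterranean diet and "in 30% of the group consuming a standard diet".

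**The concern.** When an outcome is measured at entry and again at 12 months, the entry value is usually its strongest single predictor. A model containing both arm and entry value removes that part of the variance and corrects for chance imbalance between the arms. The plan names no such model. Its only adjusted model has categorised outcomes, and it does not fix the baseline value as a covariate: selection by bivariate significance may or may not bring it in.

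Two further features leave the analysis open. The text does not say whether the t test and Mann-Whitney test are applied to 12-month values or to changes from baseline, and the two differ in precision. The normality check also means that one outcome may be reported as a difference in means and the next as a comparison of ranks, a choice made only once the data are seen.

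At stake is precision on several continuous endpoints in a trial of 120 patients, and a clear statement of what is estimated for each.

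**Working it through.** **Inputs from the protocol.** 58% versus 30%; 95% confidence, taken as two-sided alpha 0.05 (sidedness is not stated); power 80%; 49 per group; losses of 20%; 60 per group enrolled.

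**Inputs that are assumptions.** A true difference of 0.40 SD in the 12-month value, and a baseline to 12-month correlation r of 0.5 to 0.9. The protocol gives neither.

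**Step 1: the plan's own figure.** Two-proportion formula, pooled variance under the null, no continuity correction, mean proportion 0.44:

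n = [1.960·√(2·0.44·0.56) + 0.842·√(0.58·0.42 + 0.30·0.70)]² / 0.28² = (1.376 + 0.567)² / 0.0784 = 48.1, rounded up to 49.

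The stated 49 per group reproduces. Power is 80.7% at 49 per group and 79.9% at 48.

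**Step 2: patients available for analysis.** 60 × (1 − 0.20) = 48 per arm.

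**Step 3: effective standardised difference by method.** With equal SDs at both visits:

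- 12-month value, unadjusted: d = 0.40.
- Change score: the SD is multiplied by √(2(1 − r)), so d = 0.40/√(2(1 − r)).
- ANCOVA: the residual SD is multiplied by √(1 − r²), so d = 0.40/√(1 − r²).

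**Step 4: power at 48 per arm** (two-sided 5%, noncentral t, noncentrality d·√(48/2)):

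| r | Unadjusted 12-month value | Change score (d) | ANCOVA (d) |
|---|---|---|---|
| 0.5 | 49% | 49% (0.40) | 61% (0.46) |
| 0.7 | 49% | 71% (0.52) | 78% (0.56) |
| 0.8 | 49% | 87% (0.63) | 90% (0.67) |
| 0.9 | 49% | 99% (0.89) | 99% (0.92) |

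If 12-month values are compared, ANCOVA gains 12, 29 and 41 points at r = 0.5, 0.7 and 0.8. If changes are compared, it gains 12, 7 and 3 points, and essentially nothing at 0.9.

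**Step 5: check by simulation** (2,000 trials per scenario, 49 per group). At 0.40 SD and r = 0.5, power was 50% for the t test on 12-month values, 51% for the t test on changes, 49% for Mann-Whitney and 62% for ANCOVA. With no true effect, rejection rates lay between about 4% and 5.5% for every method, so each test taken alone is valid. On these normal data, Mann-Whitney lost only about 1 to 3 points to the t test. The normality gate therefore costs little power; its harm is that the estimand is not fixed in advance.

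**Step 6: what the cut alone costs.** On one underlying normal scale with equal SDs and a common cut-off, 58% versus 30% corresponds to z(0.58) − z(0.30) = 0.202 + 0.524 = 0.726 SD. At 48 per arm a t test on that scale has 94% power, against 80% for the two proportions.

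**The case against.** **The design is about proportions.** The sample size compares two proportions, and the Results section states the expectation as a higher proportion of indicators in control. The weight-loss comparison keeps its planned power of about 80%. This stands: the proportion analyses belong in the plan and should remain.

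**The t test may use changes.** The sample size speaks of weight loss, the QSQ outcome is worded as a change, and the Discussion expects a loss relative to initial weight. A change score does use the baseline. This also stands. A reader might infer that the plan ignores baseline altogether, or that the gain is always from 49% to as much as 90%. The text supports neither: it leaves the choice open, and the larger gain applies only if raw 12-month values are compared.

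**The 94% is not lost.** A reader might take 94% versus 80% as power that the plan throws away. The 94% belongs to an unadjusted t test on the continuous scale, which the plan already names beside the chi-square test.

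**Patients at goal on entry, and the QSQ cut-point.** One might argue that patients already in control at entry dilute the comparison, or that quality of life cannot enter a logistic model without a cut-point. Both depend on definitions that an article may leave to the full protocol, and no proportion at goal on entry is given. Neither is relied on here.

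**The methods are valid.** Agreed. Randomisation makes baseline imbalance a matter of chance, not bias. The point is efficiency and prespecification.

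**Conclusion.** The point holds as one of efficiency and prespecification. No stated analysis conditions on the outcome's baseline value, although that value is collected; the text does not settle whether values or changes are compared; and the choice between means and ranks is left to the data.

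For an assumed 0.40 SD difference at 48 per arm, the gain from ANCOVA is 12 to 41 points of power over unadjusted 12-month values for r from 0.5 to 0.8. Over change scores it is 12 points at r = 0.5, falling to 3 at r = 0.8 and to about nil at r = 0.9. For outcomes that track closely over time, as weight may, ANCOVA would add little to a change score. These sizes rest on the assumed effect and correlations and on equal SDs at the two visits.

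The mean paired with an IQR is a descriptive slip with no effect on inference.

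**What to change.** 1. For each continuous outcome (weight, glucose, each lipid, waist, body composition, ESS total, QSQ scores), prespecify ANCOVA of the 12-month value on arm and baseline value. Report the adjusted mean difference with its 95% CI.
2. Name in advance the variables to be log-transformed, such as triglycerides, and drop the Kolmogorov-Smirnov gate.
3. Keep the proportion analyses, including the weight-loss proportion on which the sample size rests. In the logistic model, fix baseline status as a covariate instead of leaving it to bivariate significance.
4. Describe skewed variables by median and IQR.

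The cost is analysis wording only: the baseline values are already scheduled, and no visit or measurement is added. Keeping the weight-loss proportion in the plan preserves its link to the sample size. Recruitment is under way and the Results section places the analysis in February 2026, so the change should be recorded and dated before any comparison by arm is seen.
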